**Fig. 2 Fig2:**
[figure not shown]
Schedule of enrollment, interventions, and assessments

At baseline all participants receive general information and recommendations about the positive effects of regular PA and less ST on the improvement of cardiovascular risk factors.

Therefore, all study subjects will receive age-appropriate literature from the Federal Centre for Health Education (BZgA) [38] and a chart from the Fonds Gesundes Österreich (FGÖ) [39]. Recommendations provided for PA are based on WHO guidelines for PA for people of age ≥ 65 years [14].

### Random allocation

After screening and accelerometry, participants will be randomized 1:1 in the intervention and the control group. The randomization will be conducted using an automated function in the documentation software.

### Study intervention

We developed a low-threshold intervention characterized by easy access to the intervention and a low effort for the target group. The intervention comprises two individualized feedback letters, automatically generated in R software (version 3.3.2, Lucent Technologies, Murray Hill, NJ, USA) from the study data base using the variables number of steps per day, time in minutes of MVPA, and sedentary time in min per day.

Participants in the intervention group will receive a feedback letter by mail shortly after wearing the accelerometer after the baseline examination and after the 3-month follow-up. The feedback letters will contain personalized feedback based on accelerometry as well as ST behavior. PA and ST data will be depicted in three comprehensive graphs:

One graph will represent the number of steps per day that participants took over the 7 days wearing the accelerometer device (Fig. 3).

**Fig. 3 Fig3:**
[figure not shown]
Graph of steps taken per day

Therein, 10,000 steps per day will be marked as a red line. Ten thousand steps, has been chosen because this number is used in several prevention programs in Germany and is well known in the population [40, 41].

The second graph will constitute intensity of PA divided into colored bar charts per day from red for sedentary activities to dark green for vigorous activities (Fig. 4).

**Fig. 4 Fig4:**
[figure not shown]
Graph intensity of physical activity (PA) per day

The third graph will show time doing moderate and vigorous activities per week, sitting time per day in percent as a weekly average, count of sit-to-stand transactions as a weekly average, and counts per day as a weekly average measure. To communicate these individual PA and ST measurements effectively to the participants, we will use a multidimensional representation using color bar charts (green represents a high PA level, red represents a low PA level) added with specific recommendations (Fig. 5).

**Fig. 5 Fig5:**
[figure not shown]
Graph of specific physical activity (PA) and sitting time (ST)

Additionally, participants receive leaflets with age-appropriate recommendations for PA and ST at baseline. The leaflets are from the Federal Centre for Health Education.

### Follow-up

The follow-up examinations after 3, 6, and 12 months will be conducted in the DZHK examination center. Following examination, PA and ST will be objectively measured by the personal accelerometer. After a period of 7 days, participants bring back the accelerometer devices. In addition, study participants receive paper-based questionnaires as shown in the flow chart in Fig. 1.

### Power calculation

The sample size estimate was based on the amount of PA (mean time in min per day), measured in a comparable group of elderly people. In the study in question (Troiano et al.) the amount of PA was on average 15 min of combined PA (moderate and vigorous PA) per day [21]. We took these data as the starting point for the estimation of the required sample size. We assume that participants in the control group remain at approximately the same level while people in the intervention group increase their amount of PA by 20% [42], which corresponds to an increase from 15 to 18 min of PA per day after 6 months. To demonstrate this effect, a total number of 151 participants is needed (standard deviation 6.0 min, alpha = 0.05, power = 0.80). Assuming a loss to follow-up of about 30%, we will recruit 216 participants.

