**Methods/design:**

MOVING is a two-arm, randomized controlled trial. Inclusion criteria are age ≥ 65 years and the ability to be physically active. Exclusion criteria are the permanent use of a wheelchair and simultaneous participation in another study on PA.

At baseline participants who give informed consent will receive general information and recommendations about the positive effects of regular PA and less ST. Participants of both groups will receive an accelerometer device, which records PA and ST over a period of seven consecutive days following by a randomization. Participants in the intervention group will receive automatically generated, individualized feedback letters by mail based on their PA and ST at baseline and at 3-month follow-up. Further follow-up examinations will be carried out at 6 and 12 months.

The primary outcome is the increase of PA and the reduction of ST after 6 months in the intervention group compared to the control group.

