### Data analysis

ActiLife software (version 6.13.2 or later, ActiGraph, Pensacola, FL, USA) will be used for data download and data processing. A valid measurement day is defined as a record of at least 10 h total wearing time and a record time of at least 4 days is required for data analysis. To categorize PA intensity, we used specific cut points based on Freedson [45]. PA is divided into sedentary (0–99 steps), light (100–1951 steps), moderate (1952–5724 steps), and vigorous (5725–9498 steps) PA. Step counts are based on 60-s epochs.

Statistical analysis will be conducted using pseudonymized data. First, the assessed project data will be descriptively analyzed. We will verify the conditions in both groups. In case of significant differences between the intervention and control group, analyses will be adapted accordingly and adjusted for relevant variables. Subsequently, the primary and secondary outcomes will be analyzed between the groups using *t* tests or corresponding non-parametric tests in case of ordinal variables or non-normality of the values. The tests will be conducted based on the intention-to-treat principle. The use of the intention-to-treat procedure ensures that each subject is included in the analysis. The analysis are carried out with the statistical software IBM SPSS Statistics (version 23.0.0.2 or later, IBM Corp., Armonk, NY, USA).

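### The sample size of 151 does not follow from the printed inputs, which give 128; an SD, power, alpha or allowance behind 151 and 216 is misstated or missing.

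*Protocol article*

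**What the plan says.** The Power calculation section takes its starting level from an earlier accelerometer survey in which "the amount of PA was on average 15 min of combined PA (moderate and vigorous PA) per day". It assumes no change in the control group and a 20% rise in the intervention group, "which corresponds to an increase from 15 to 18 min of PA per day after 6 months". It then concludes: "To demonstrate this effect, a total number of 151 participants is needed (standard deviation 6.0 min, alpha = 0.05, power = 0.80"). The recruitment target follows: "Assuming a loss to follow-up of about 30%, we will recruit 216 participants".

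Two other inputs stand elsewhere in the article. Random allocation says that "participants will be randomized 1:1 in the intervention and the control group". Data analysis plans between-group t tests, "tests or corresponding non-parametric tests in case of ordinal variables or non-normality of the values".

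The Power calculation section does not say whether alpha is one- or two-sided. It mentions no adjustment for multiple outcomes, no allowance for a rank test or for invalid recordings, and no inflation other than the 30% for loss to follow-up.

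**The concern.** Difference, SD, alpha, power and allocation ratio together fix the sample size of a two-group comparison of means. The article prints all five and presents 151 as their result. A standardised effect of 0.5 with 80% power at two-sided 0.05 gives 128, so 151 stands out at once. An odd total under 1:1 allocation is a minor further sign that the figure did not come straight from a per-arm calculation.

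At stake is what the trial was designed to detect. If SD 6.0 is right, the trial has more power than stated, and part of the recruitment target has no justification in the text. If the SD used was nearer 6.5, the printed SD is wrong and there is no spare power. If an allowance or a smaller alpha was used, the reader needs it to judge whether the planned analysis matches the design. The text does not allow these cases to be told apart.

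**Working it through.** **Inputs**

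- Difference: 18 − 15 = 3 min/day (Power calculation).
- SD 6.0 min, alpha 0.05, power 0.80 (Power calculation).
- Allocation 1:1 (Random allocation).
- Test: two-sample t test (Data analysis).
- Loss to follow-up 30% (Power calculation).
- Sidedness is not stated; two-sided is assumed and one-sided is also tried.

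**The plan's own last step.** 151 / (1 − 0.30) = 215.7, rounded up to 216. This reproduces.

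**The step from the inputs to 151**

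- Standardised effect: d = 3 / 6.0 = 0.5.
- Normal approximation, two-sided: n per arm = 2 × (1.96 + 0.8416)² / 0.5² = 62.8, so 63 per arm, 126 in total.
- Noncentral t, two-sided: 63.8 per arm, so 64 per arm, 128 in total.
- One-sided: 50 per arm (normal) or 51 (t), so 100 to 102 in total.

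None of these is 151. The ratio 151/128 is 1.18.

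**What 151 delivers on the printed inputs.** With about 75.5 per arm, d × √(n/2) = 0.5 × √37.75 = 3.07. Power is then about Φ(3.07 − 1.96) = 0.867 by the normal approximation, and 0.863 for the t test: 86%.

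**What would make 151 the answer at 80% power (two-sided t test, changing one input at a time)**

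- SD of about 6.54 instead of 6.0; or
- a difference of about 2.75 min instead of 3; or
- two-sided alpha of about 0.027 instead of 0.05.

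**Unstated routes to 151 or close to it**

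| Route | Total |
|---|---|
| 15% allowance: 128 / 0.85 | 150.6, rounded up to 151 |
| 20% added to the normal-approximation figure: 126 × 1.20 | 151.2 |
| Rank test at relative efficiency 0.864 | 148 |
| Alpha 0.025, e.g. for two primary outcomes | 154 (normal), about 155 (t) |
| Power 0.85 | 146 (t) |
| Power 0.90 | 172 (t) |

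A misprint of one of the two common higher power values therefore does not explain 151. The two allowance routes do reach it, but the article mentions neither.

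**Recruitment from the printed inputs.** 128 / 0.70 = 182.9, so 183, which is 33 fewer than 216.

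**The case against.** The strongest reply is that the discrepancy does no harm. On the printed inputs 151 exceeds what is needed, power is 86%, and 216 follows correctly from 151. If the SD was really about 6.5, the stated 80% holds and one printed digit is wrong. If an allowance was built in, only its mention is missing, and a condensed article could have dropped it. Data analysis does foresee non-parametric tests, and 128/0.85 rounds up to exactly 151, so a deliberate inflation is plausible. In all of these cases the planned number still meets the 80% target.

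Much of this stands. The discrepancy does not leave the trial underpowered, and 151 does give at least 80% power at SD 6.0; what fails is the statement that 151 is the number needed for 80%. The list of possible causes must also stay open: besides the SD, the power and an allowance, a reduced alpha for the two outcomes (activity and sitting time) named as primary comes close.

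It does not remove the point. The article attaches 151 directly to the inputs in the parenthesis, so this is a stated result that its own inputs do not produce, rather than a detail left to a fuller document. The candidate explanations also have different consequences: a larger SD means no spare power, a rank-test allowance bears on the choice of test, and a smaller alpha would contradict the printed 0.05.

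**Conclusion.** The concern holds. From the printed inputs the required total is 128 for a two-sided t test with equal arms and a common SD of 6.0 (126 by the normal approximation, 102 for a one-sided t test). The stated 151 is 18% above 128, far beyond rounding or differences between programs. If SD 6.0 and two-sided alpha 0.05 are correct, 151 evaluable participants give 86% power for 3 min, or 80% power for about 2.75 min, and 183 recruits would have been enough. If they are not correct, the printed SD, alpha or set of allowances is wrong or incomplete. The document cannot settle which, and the allowance routes that reach 151 remain conjecture. The error lies only between the inputs and 151; the step to 216 is sound. Because the recruitment target rests on 151, the paragraph has to be corrected, although the number recruited need not change.

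**What to change.** Keep 216 and check the original calculation to see which inputs were used. Then do one of the following.

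- **If SD 6.0 and alpha 0.05 (two-sided) are the true inputs**, restate the paragraph along these lines: *128 evaluable participants (64 per arm) give 80% power to detect 3 min/day with SD 6.0 at two-sided alpha 0.05. Recruiting 216 with 30% loss leaves about 151 evaluable (216 × 0.70 = 151.2), which gives 86% power.*
- **If 151 came from another SD, a smaller alpha, or an allowance** (for example for a rank test or for invalid recordings), print that input and show how it leads to 151. The 86% figure should not be printed in this case unless it is recalculated for those inputs.

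Either way, state the sidedness of alpha. The cost is the rewording of one paragraph; recruitment does not change.

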### Documentation, data storage, data security, and data protection

Participants’ sociodemographics (age, sex, education), lifestyle parameters (nutrition habits, smoking, and alcohol-drinking behavior) from the paper-based questionnaires (self-report) are documented using the Cardiff TeleForm system® (Electric Paper, Lüneburg, Germany). The questionnaires and the daily diary protocol contain 1-D barcodes to ensure anonymization. Somatometry data and blood pressure measurements will be documented in eCRFs in an IT-supported documentation system including automatic plausibility and completeness checks [43]. The documentation system is based on the concept of offline clients, each staff member in the examination center has individual login data [43].

After merging the data assessed in the examination center with the PA data from the accelerometer and the data from the paper-based questionnaires, all data will be stored in a central project data base. The data storage is managed according to current standards for data security and data privacy, documented in the institutional data protection concept of the Institute for Community Medicine [44]. Only the staff members in the examination center have access to personal data during baseline and follow-up examinations.

In addition, all participants receive a study ID card including an 1-D barcode at the baseline examination to support the correct assignment of the participants to their data over time.

### Data analysis

ActiLife software (version 6.13.2 or later, ActiGraph, Pensacola, FL, USA) will be used for data download and data processing. A valid measurement day is defined as a record of at least 10 h total wearing time and a record time of at least 4 days is required for data analysis. To categorize PA intensity, we used specific cut points based on Freedson [45]. PA is divided into sedentary (0–99 steps), light (100–1951 steps), moderate (1952–5724 steps), and vigorous (5725–9498 steps) PA. Step counts are based on 60-s epochs.

Statistical analysis will be conducted using pseudonymized data. First, the assessed project data will be descriptively analyzed. We will verify the conditions in both groups. In case of significant differences between the intervention and control group, analyses will be adapted accordingly and adjusted for relevant variables. Subsequently, the primary and secondary outcomes will be analyzed between the groups using *t* tests or corresponding non-parametric tests in case of ordinal variables or non-normality of the values. The tests will be conducted based on the intention-to-treat principle. The use of the intention-to-treat procedure ensures that each subject is included in the analysis. The analysis are carried out with the statistical software IBM SPSS Statistics (version 23.0.0.2 or later, IBM Corp., Armonk, NY, USA).

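### Covariate adjustment depends on whether the randomised groups differ significantly, so chance selects the model and most of the gain from the baseline measurement can be lost

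*Protocol article*

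**What the plan says.** The Data analysis section of the protocol article sets out a sequence. The data are first described. Then: "We will verify the conditions in both groups". Next comes the conditional rule: "In case of significant differences between the intervention and control group, analyses will be adapted accordingly and adjusted for relevant variables". The outcome comparison comes only after this step. It is based on the t test, with an alternative for data that do not suit it: "tests or corresponding non-parametric tests in case of ordinal variables or non-normality of the values".

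The section does not say which variables are compared, at what level, what makes a variable relevant, or which model would do the adjusting. No other section fixes a covariate set.

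Two other places matter. Random allocation states: "After screening and accelerometry, participants will be randomized 1:1". Accelerometer PA and ST, the same measures as the primary outcome, therefore exist for both arms before allocation. The abstract's Methods/design paragraph defines the endpoint: "The primary outcome is the increase of PA and the reduction of ST after 6 months in the intervention group compared to the control group". This can be read as a comparison of 6-month values or of changes from baseline.

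**The concern.** When allocation is random, a significance test on a baseline variable tests a hypothesis already known to be true. It says nothing about whether adjustment would help. Three consequences follow.

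- Whether the primary analysis is adjusted is settled by chance after the data are in, not by design.
- Significance of an imbalance does not measure prognostic strength. A strong predictor of 6-month MVPA with a non-significant imbalance is left out.
- In most trials run this way the default test applies, and it does not adjust for baseline accelerometry, probably the best predictor available.

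At stake are precision that costs nothing to obtain, and a primary model that can be identified before the data are seen.

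**Working it through.** **Inputs from the Power calculation section.** Difference 3 min/day ("which corresponds to an increase from 15 to 18 min of PA per day after 6 months"), SD 6.0, alpha 0.05 (sidedness not stated; two-sided assumed), power 0.80, 151 analysed, 30% loss, 216 recruited. Standardised difference d = 3/6 = 0.5.

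**The plan's own figure.** The normal approximation gives n per arm = 2(1.96 + 0.842)²/0.5² ≈ 62.8, so 63 per arm and 126 in total (128 with the exact t test). The stated 151 is not reproduced from these inputs. The dropout step is: 151/0.70 = 215.7, so 216. With 151 analysed, unadjusted power is about 0.86–0.87. The gap between 126–128 and 151 does not affect the present point. About 75 per arm is used below.

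**How often the trigger fires by chance.** For k independent baseline tests at 5%, P(at least one significant) = 1 − 0.95^k: 5% for k = 1, 23% for 5, 40% for 10, 64% for 20. The number of variables is not stated, and correlation among them would lower these figures.

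**Power by formula.** The baseline-outcome correlation r is not in the documents, so a range is assumed. With n = 75 per arm, d√(n/2) = 0.5 × √37.5 = 3.062.

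- Unadjusted 6-month values: Φ(3.062 − 1.96) = 0.865.
- ANCOVA: Φ(3.062/√(1 − r²) − 1.96) = 0.894, 0.942, 0.969, 0.990 for r = 0.3, 0.5, 0.6, 0.7.
- Unadjusted change scores: Φ(3.062/√(2(1 − r)) − 1.96) = 0.735, 0.865, 0.928, 0.977.

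**Power of the rule by simulation** (bivariate normal, one covariate, ANCOVA used only if the baseline p is below 0.05):

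| Assumed r | Prespecified ANCOVA | Rule, 6-month values | Rule, change scores |
|---|---|---|---|
| 0.3 | 89% | 86–87% | 75% |
| 0.5 | 94% | 87% | 87% |
| 0.6 | 97% | 87–88% | 93% |
| 0.7 | 99% | 88% | 98% |

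With one covariate the trigger fires in only 5% of trials, so the rule stays close to the unadjusted test.

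**Type I error.** Overall null rejection under the rule on 6-month values is about 3–5%, lower as r rises. Prespecified ANCOVA is at about 5%.

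**Conditional behaviour.** Take null trials with baseline |z| above 1.5 but not significant (about 8% of trials). The rule does not adjust these. The unadjusted test of 6-month values rejects in roughly 7, 10, 12 and 14% for the four values of r (6–15% allowing for simulation error). Change scores reject in about 8–12%. ANCOVA stays near 5%.

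**The case against.** Several objections are fair, and they limit the point.

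- **A reader might infer that false positives are inflated.** They are not, overall: the rule is slightly conservative. The conditional excess belongs to any unadjusted test at that degree of imbalance and is offset where balance is good (about 3% rejection at r = 0.6 when |z| is at most 1.5). The trigger removes the most extreme cases. Inflation could arise if relevance were judged after seeing outcomes, but the article does not say that it will be.
- **A reader might infer a contradiction, because t and rank tests take no covariates.** The wording about adapting the analyses can naturally mean switching to an adjusted model. That model is unnamed, which an article may leave to an analysis plan.
- **A reader might infer that irrelevant variables would be adjusted for.** The text confines adjustment to relevant ones, and a plan not shown might list them.
- **Planned power is met under the rule on 6-month values,** at 86–88% against 80%. This stands. With change scores it does not at r = 0.3 (about 75%).
- **The one-covariate simulation may understate how often adjustment happens.** If any of ten independent variables triggered a model that includes baseline MVPA, power at r = 0.6 would be about 0.40 × 0.97 + 0.60 × 0.865 ≈ 91%, still below 97%.
- **The section never says baseline,** and verifying conditions could mean checking test assumptions. But the trigger is a difference between groups, examined before the outcome tests, so baseline comparability is the natural reading.

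None of this defends the trigger itself. It is a rule that the article states, not a detail that it omits.

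**Conclusion.** The point holds as one of efficiency and prespecification. Making adjustment conditional on a significant group difference leaves the choice of model to chance and gives up most of what the pre-randomisation accelerometry could contribute if 6-month values are compared. On that reading the loss against prespecified ANCOVA is about 2–3 percentage points of power at r = 0.3 and about 11 at r = 0.7. On change scores it is about 14 points at r = 0.3 and about 1 at r = 0.7. ANCOVA is at least as good throughout the range.

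The figures rest on assumed correlations, normal data, one covariate, 75 analysed per arm, and the plan's d of 0.5. The trial is not invalidated, and no claim of excess overall type I error is supported. Inference is less reliable in the roughly 8% of trials with moderate, non-significant imbalance.

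**What to change.** Delete the significance trigger. Name one primary model, such as ANCOVA of 6-month MVPA on arm and baseline MVPA, with the same form for ST. Add at most a short named list of covariates already collected, such as age and sex, and use them whatever balance is observed. Present baseline data descriptively, without tests. Keep the t or rank test as a sensitivity analysis.

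This costs a sentence or two in the protocol or analysis plan, settled before the outcome data are examined. It needs no new data and no extra participants.

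### The primary model is chosen by two checks on the data (baseline significance and normality), and by default it does not use the pre-randomisation accelerometry as a covariate

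*Protocol article*

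**What the plan says.** The protocol article fixes the following.

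- **Test (Data analysis).** Primary and secondary outcomes are compared between groups by t test, "or corresponding non-parametric tests in case of ordinal variables or non-normality of the values". No normality test or threshold is named.
- **Adjustment (Data analysis, just before the test).** The two groups are first compared. If they differ significantly, the analyses are adapted and adjusted for relevant variables, which are not listed.
- **Baseline data.** The abstract states: "Participants of both groups will receive an accelerometer device, which records PA and ST over a period of seven consecutive days". The abstract and the Random allocation section both place this week before the 1:1 randomisation.
- **Outcome (abstract and Research objectives).** The primary outcome is worded as an increase of PA and a reduction of ST after 6 months. Neither place says whether the 6-month value or the change from baseline is compared.
- **Sizing (Power calculation).** The target is a 20% rise, "which corresponds to an increase from 15 to 18 min of PA per day after 6 months", with "standard deviation 6.0 min, alpha = 0.05, power = 0.80". The article then states that "a total number of 151 participants is needed". It does not say whether the SD belongs to the 6-month value or to the change.

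**The concern.** Two features of the data decide the primary analysis: whether a baseline comparison reaches significance, and whether the outcome looks normal. The form of the primary result is therefore not known until the data have been inspected.

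The baseline rule picks covariates for the wrong reason. Under valid randomisation a 5% test of baseline PA is significant in about 5% of trials. In the other 95% or so the rule leaves baseline PA out, although it is likely to be among the strongest predictors of PA at 6 months. The case for adjusting rests on that prediction, not on chance imbalance.

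The normality rule can change what is estimated. The trial is sized on a difference in mean min/day. A standard two-sample rank test does not estimate that difference, and the article names no companion estimate. Minutes of MVPA cannot fall below zero, so right skew, and hence a switch to the rank test, is plausible.

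At stake are precision and a result on the scale the trial was designed for. The validity of the randomised comparison is not in question.

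**Working it through.** **Inputs from the Power calculation.** Difference 18 − 15 = 3 min/day; SD 6.0, so d = 3/6 = 0.5; alpha 0.05 (taken as two-sided; sidedness is not stated); power 0.80; 151 evaluable, or 75.5 per arm.

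**The plan's own figure.** n per arm = 2 × (1.960 + 0.842)² × 6²/3² = 62.8, so 63 per arm and 126 in total. The t-test version gives 63.8 per arm, so 128. The stated 151 does not follow from these inputs; that is a separate point. The attrition step does reproduce: 151/0.70 = 215.7, so 216. I take 151 as given below.

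**Power of the default test at 151.** Noncentrality = 0.5 × √(75.5/2) = 3.07. The normal approximation gives Φ(3.07 − 1.96) = 0.867, and the noncentral t gives 0.863, or about 86%.

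**Using baseline.** The baseline to 6-month correlation r is not in the documents, so it is assumed. With SD 6.0 at both times:

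- ANCOVA: residual SD = 6 × √(1 − r²), effect = 0.5/√(1 − r²).
- Change score: SD = 6 × √(2(1 − r)), effect = 0.5/√(2(1 − r)).

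| r (assumed) | Residual variance, ANCOVA | ANCOVA effect | ANCOVA power | Change-score effect | Change-score power | Unadjusted power |
|---|---|---|---|---|---|---|
| 0.3 | 91% | 0.524 | 89% | 0.423 | 73% | 86% |
| 0.5 | 75% | 0.577 | 94% | 0.500 | 86% | 86% |
| 0.6 | 64% | 0.625 | 97% | 0.559 | 93% | 86% |
| 0.7 | 51% | 0.700 | 99% | 0.645 | 98% | 86% |

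Powers are two-sided t-test values at 75.5 per arm. ANCOVA does at least as well as either alternative in every row. A change-score test is worse than ignoring baseline when r is below 0.5.

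**If the outcome is skewed.** The table compares ANCOVA with a t test on normal data, but with skewed data the plan would use a rank test, so that is the relevant comparator. Simulation under an assumed lognormal shape (means 15 and 18, SD 6 in both arms, 75 per arm) gave about 85% power for the t test, 92–94% for the rank test, and 93% / 96–97% / 98% for ANCOVA at r = 0.5 / 0.6 / 0.7. The gain over the rank test is then roughly 0 to 5 points. This comparison is specific to equal SDs in the two arms.

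**How likely the switch is.** With lognormal 6-month values of mean 15 and SD 6, a Shapiro-Wilk test rejects in at least one arm in about 98–99% of simulated trials. For change scores the proportion falls to roughly 60%. The article names no normality test, so these figures show that the switch is likely under that shape, not that it is certain.

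**If the SD is larger than planned.** These SDs are also assumed. At 151 evaluable, SD 8 gives 63% power unadjusted, against 75% (r = 0.5) and 89% (r = 0.7) with ANCOVA. SD 10 gives 45%, against 56% and 73%.

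**The case against.** The strongest reply is that the plan is sound as written. A two-sample t test in a randomised trial is unbiased for the mean difference, and on the stated inputs it has 86% power against a target of 80%. That stands. A reader might infer that the primary analysis is invalid or the trial underpowered for want of baseline adjustment; the documents do not support either. Power falls below 80% at 151 only if the SD exceeds about 6.6 min/day, and the article gives no such figure.

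A reader might also infer that baseline is never used. That goes too far on two counts. The Data analysis section provides for adjustment after a significant group difference, so the comparison is unadjusted by default, not always. And an increase in PA may mean change from baseline, in which case a t test on change already uses it. At r = 0.6 or 0.7 that test comes within 4 points and 1 point of ANCOVA. Neither count removes the point: the adjustment rule is data-driven with unnamed variables, and the article does not settle whether change is tested.

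It would be too strong to say that a rank test cannot use baseline or yield min/day. Rank ANCOVA and rank tests on change scores exist, and a Hodges-Lehmann shift or descriptive means could be reported alongside; an article may leave such companion estimates to the analysis plan. What stands is narrower: the standard two-sample rank test does not adjust for baseline or estimate the mean difference used for sizing.

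Finally, a large loss of power cannot be claimed from the normal-theory table while also expecting skewed data. Against the rank test in the lognormal scenario, the gain is small.

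**Conclusion.** The point holds as one of efficiency and of an unfixed estimate, not of validity. The article states its method, and that method lets two checks on the data select the primary model, leaves baseline out as a covariate by default although it is measured before randomisation, and does not say whether level or change is tested.

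The direction is secure: under the equal-SD model used here, ANCOVA is at least as efficient as the unadjusted and change-score t tests for any r from 0 upwards. The size is not secure, because r is not in the documents. With normal data and r of 0.5 to 0.7, the gain at 151 evaluable is about 8 to 13 points over an unadjusted t test and about 1 to 8 points over a change-score test. With lognormal data and equal SDs it is about 0 to 5 points over the rank test. The stronger reason to change is that a single fixed model gives one pre-stated result in min/day with an interval. It should be changed, since the improvement uses data already collected.

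**What to change.** Pre-specify one primary model: 6-month MVPA (min/day) regressed on arm and baseline MVPA, with robust or bootstrap confidence intervals to cope with skew. Use it whatever a baseline comparison or a normality check shows, and report the adjusted difference in min/day with its interval. This also settles the level-or-change question, because with baseline in the model the estimated group difference is the same for either.

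Delete the significance-triggered adjustment rule. Apply the same model to ST and to the continuous secondary outcomes, each with its own baseline value. Keep the rank test as a sensitivity analysis.

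The cost is analysis wording only, with no new data. The change should be made and dated before outcomes are examined by group.
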